## Trial design {8}

Investigator-initiated, randomised, controlled, investigator-blinded, pragmatic superiority trial with a parallel group design, 1:1 concealed allocation ratio and a 28-day main follow-up period.

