#### Outcomes rational

Based on the best current evidence [4, 9], we expect any difference in efficacy between intervention and control to be due to a difference in intubation rate and/or possibly time in respirator rather than survival. Respirator use is a particularly clinically relevant outcome during the current COVID-19 pandemic when ICU beds are scarce. The benefit of choosing VFD as a primary outcome rather than intubation frequency is that VFD strongly penalises death. Hereby, VFD effectively assesses our primary concern for harm related to the intervention, namely, an adverse delay to intubation leading to reduced survival. The drawback of VFD is a potential dilution of harm (death) due to high efficacy (intubation rate) which is why we are also including days alive within 28 and 180 days as secondary outcomes. The 180 days mortality outcome will not be reported in the primary manuscript because we do not wish to delay dissemination of findings, but we consider it necessary to evaluate since many patients with COVID-19 have prolonged hospital stay. SpO2/FiO2 ratio is included as a sort of proof of concept outcome with the purpose of confirming or rejecting our underlying assumption that the higher PEEP enabled by the Helmet CPAP will improve lung aeration. We also have a patient-centred outcome regarding self-reported comfort. Both devices are reported to have superior tolerance compared to low-flow oxygen therapy and CPAP masks but they have never been tested head-to-head in adults. Device comfort may be particularly important if the trial does not show superiority or if the effect size is small. Lastly, we have included a secondary outcome on carbon dioxide rebreathing which, according to our judgement, is the main harm apart from death and comfort/tolerance issues that can be considered more likely for the intervention group than the control group. We are taking measure to avoid this from happening (i.e. minimum Helmet CPAP air flow 40 L/min).

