### Sample size {14}

We have estimated a required sample size of 120 patients (60 per group) to achieve 90% power to detect superiority at a 0.05 significance level. This estimate is based on the following clinical assumptions and statistical calculations:
A median of 1 out of 3 patients started on HFNC or Helmet CPAP will be started on invasive mechanical ventilation [2].Patients put on the ventilator will be treated in the ward for median 2.3 days before intubation, and ventilated patients will have 67.4% ICU mortality, and those who survive will stay on the ventilator for a median of 6 days [13].Patients not put on the ventilator will have 8.1% 28-day mortality and survive for a median of 7.5 days [2].The Helmet CPAP will avoid 3 out of 5 intubations compared to HFNC, which is an estimate based on (A) Frat et al. [4] who reported 40/106 (38%) intubation frequency in HFNC treated patients with AHRF versus 55/110 (50%) in patients with CPAP masks (*p* = 0.18 for comparison) and (B) Patel et al. [9] who reported 24/39 (61.5%) intubation frequency in patients with ARDS treated with CPAP mask versus 8/44 (18.2%) treated with Helmet CPAP (*p* < 0.001 for comparison). Hence, we expect treatment with Helmet CPAP to require (18.2/61.5)/(38/50) ≈ 2 out of 5 intubations compared to HFNC.

This leads to an estimated VFD of 19.545 for patients on HFNC (calculation: ((2/3*0.919*28) + (1/3*0.326*22))) and 23.257 for patients on Helmet CPAP (calculation: ((13/15*0.919*28) + (2/15*0.326*22))). We assume the standard deviation (SD) to be 6 in both groups based on a mean estimate of SDs reported from five trials with VFD as the primary endpoint in the paper by Yehya et al. [14]. Because we expect a reduction of intubation frequency and days in ventilator to be the driving factor behind a reduction in VFD rather than mortality, we will use Mann-Whitney *U* test as the primary statistical method, also based on argumentation by Yehya et al. [14]. In order to estimate the sample size, data was simulated with mean 23.257 for the intervention group and mean 19.545 for the control group, the standard deviation was set to 6 for both groups, and then the sample size was varied by simulation until the proportion of significant (0.05) two-sided Mann-Whitney *U* test was equal to the desired power (0.90) using R statistical software (See Additional file 1 for R code). This resulted in a required sample size of 60 patients per group.

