## Statistical methods

### Statistical methods for primary and secondary outcomes {20a}

#### Primary outcome

We will analyse VFD as a continuous outcome between two groups with a non-normal distribution using the Mann Whitney *U* test. We will provide the absolute median difference in VFD between groups with 95% confidence intervals (CI). We will also calculate and present the Mann-Whitney (ϕ) parameter with 95% CI using the R function wmwTest in the asht R package as suggested by Fay et al. [21]. We will also perform a sensitivity analysis of the primary outcome using unadjusted competing risks regression [14]. We hypothesise that the intervention group (Helmet CPAP) will have a significantly (*p* < 0.05) higher VFD than the control group (HFNC).

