#### Secondary outcomes

SpO2/FiO2 ratio (a) and patient comfort (b) will also be analysed as continuous outcomes between two groups with the Mann Whitney *U* test. Frequency of endotracheal intubation (c) and carbon dioxide rebreathing (d) are dichotomized outcomes between two groups and will be analysed using a chi-squared test (unless groups are less than 5, then we will use Fisher’s exact test). Days alive within 28 (e) and 180 days (f) from randomisation will be visualised using a Kaplan-Meier plot and analysed using unadjusted Cox regression. We will test proportional hazards assumption using a global test, Schoenfeld residuals, and a log-log plot of survival. We will use Stata MP 16.1 statistical software.

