### Adverse event reporting and harms {22}

The Swedish Medical Products Agency (Läkemedelsverket) has reviewed the study design in May 2020 and concluded that it should not be considered a clinical trial in the traditional sense but rather a pragmatic randomised study between two approved medical devices. Hence, reporting of adverse events will not be as ambitious as a clinical trial testing a novel drug. We will aim to evaluate any harm from the intervention in our primary and secondary endpoints on survival, intubation frequency, carbon dioxide rebreathing and patient-reported comfort. There is also a commentary section in the study-specific CRFs where study nurses can report allocation violations or any unexpected side-effects from allocated intervention.

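### Carbon dioxide rebreathing, the harm the protocol singles out for the helmet, is given only a significance test; with 60 per arm it needs a risk ratio and risk difference with 95% confidence intervals

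*Protocol article*

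**What the plan says.** The outcome is binary: a venous pCO2 above 6 kPa at any time in the 28 days after randomisation (Outcomes {12}). The Outcomes rational section explains its place: in the authors' judgement it "is the main harm apart from death and comfort/tolerance issues that can be considered more likely for the intervention group". The Objectives {7} section frames the question as the relative incidence of rebreathing under helmet versus HFNC. The harms section makes it part of the safety assessment: "We will aim to evaluate any harm from the intervention in our primary and secondary endpoints on survival, intubation frequency, carbon dioxide rebreathing", together with patient-reported comfort.

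For the analysis, the Secondary outcomes paragraph of section {20a} states that this outcome is one of two for which the following applies: "carbon dioxide rebreathing (d) are dichotomized outcomes between two groups and will be analysed using a chi-squared test". The only qualification is "unless groups are less than 5, then we will use Fisher’s exact test". No risk ratio, risk difference or confidence interval is mentioned. For the primary outcome the same section does commit to an estimate with an interval: "We will provide the absolute median difference in VFD between groups with 95% confidence intervals (CI"), and it adds the Mann-Whitney parameter with its own interval.

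**The concern.** The objective asks how much more often rebreathing occurs with the helmet. A chi-squared or Fisher p-value does not answer that. The gap matters more here than for an ordinary secondary outcome, because the protocol describes adverse event reporting as less ambitious than in a drug trial, plans no interim analysis and has no data monitoring committee. Much of the harm assessment therefore rests on the listed endpoints.

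The trial was sized for ventilator-free days, not for rebreathing. If rebreathing is uncommon, a non-significant test is the likely result even when the helmet truly doubles the risk. Without an interval beside the p-value, a reader cannot see which excess the data leave open.

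**Working it through.** **Inputs from the Protocol article.** 60 patients per group, 1:1, alpha 0.05 (Sample size {14}, Trial design {8}). Chi-squared test, or Fisher's test when "unless groups are less than 5, then we will use Fisher’s exact test" (Secondary outcomes, {20a}).

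**Assumptions.** The documents give no expected rebreathing rate, so HFNC risks of 5% to 25% are tried. A low rate is plausible, since patients with pCO2 above 6 kPa are excluded at entry and a minimum helmet flow is set, but that is inference. The test is taken as two-sided and the chi-squared as uncorrected. The small-count rule can mean any observed cell below 5 or any expected cell below 5, so both are computed.

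**Step 1: the plan's own sample size.** The plan says that "data was simulated with mean 23.257 for the intervention group and mean 19.545 for the control group, the standard deviation was set to 6" in each arm. The difference is 23.257 − 19.545 = 3.712.
- t-test approximation: n = 2 × (1.960 + 1.282)² × 6² / 3.712² ≈ 55 per arm.
- Divided by the Mann-Whitney efficiency 3/π = 0.955, this gives 57.6 per arm.
- Simulation (20,000 runs per n) gives power of 89.6% at 58, 90.2% at 59 and 90.6% at 60.

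The stated 60 per group reproduces for ventilator-free days.

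**Step 2: what 60 per arm gives for rebreathing.** Power is the sum, over all 61 × 61 possible tables (x helmet events, y HFNC events), of Bin(x; 60, p1) × Bin(y; 60, p0), counting tables with p < 0.05.

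| HFNC vs helmet risk | Power, observed-count rule | Power, expected-count rule |
|---|---|---|
| 5% vs 10% | 8.8% | 13.8% |
| 5% vs 15% | 33.2% | 43.8% |
| 10% vs 20% | 29.4% | 32.6% |
| 15% vs 30% | 51.3% | 51.4% |
| 20% vs 40% | 68.4% | 68.4% |
| 25% vs 50% | 81.8% | 81.8% |

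So a doubling is missed in about 86–91% of trials at an HFNC risk of 5%, in about 67–71% at 10%, in about half at 15%, and in about 32% at 20%. For 80% power against a doubling, the normal approximation requires 435 per arm at 5% and 199 per arm at 10%.

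**Step 3: what an interval would add.**
- *3/60 vs 3/60.* The p-value is 1.0. The Wilson limits for 3/60 are 0.0171 and 0.1370. The Newcombe upper limit for the difference is 0 + √[(0.1370 − 0.05)² + (0.05 − 0.0171)²] = 0.093, or +9.3 percentage points. The score interval for the risk ratio has an upper limit of 4.2.
- *Helmet 8/60 vs HFNC 3/60.* The expected count per arm is (8 + 3)/2 = 5.5. The expected-count rule therefore gives chi-squared, p = 0.11. The observed-count rule gives Fisher, p = 0.20. The upper limits are +19.7 points and a ratio of 9.0.

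In both cases the p-value is unremarkable, while the interval shows that a several-fold excess is not excluded.

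**The case against.** The strongest reply is that this is condensed reporting and not an error. A journal protocol often leaves the effect measure and interval method for binary secondary outcomes to the analysis plan, which is not shown. The same paragraph names no effect measure for SpO2/FiO2, comfort or intubation either. Chi-squared with a Fisher fallback is a standard test for a two-by-two table. The outcome is defined as a frequency, so counts per arm will presumably be reported, and from those a reader can form a ratio. Low power for a secondary harm is expected in a trial sized for another endpoint, and an interval adds no power.

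Much of this stands. It does not remove the point, because the article does not defer the analysis of rebreathing. It states one, and that analysis does not match the stated objective for the harm on which the authors themselves place weight.

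Three stronger readings are tempting, and the documents do not support them. A reader might infer that a non-significant test will be declared as no difference. No section says so, and the Discussion acknowledges that small but clinically important differences may be missed. A reader might infer that frequencies will be withheld. Nothing says that either. And a reader might conclude that a doubling would usually be missed whatever the rate. That fails at HFNC risks of about 15% and above, and the true rate is not given.

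**Conclusion.** The point holds in a limited form: a relative-incidence objective, for the harm the protocol singles out for the helmet, is paired with a test and no estimate or interval. How much that matters depends on an HFNC rebreathing rate that the documents do not state. If the rate is about 5–10%, the planned test detects a true doubling in only about 9% to 33% of trials, with the small-count rule accounting for part of that range. At 20% it detects it in about 68%. The value of the interval does not depend on guessing the rate: whatever the counts, it shows the largest excess that the data do not exclude. This is a wording change worth making. It is not a flaw in the design or in the sample size for the primary outcome.

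**What to change.** In the Secondary outcomes paragraph of section {20a}, or in the analysis plan if it is silent on this:

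- Make the analysis of outcome (d) the number and proportion per arm, with the risk ratio and risk difference (helmet vs HFNC) and 95% confidence intervals, for example score for the ratio and Newcombe for the difference.
- Keep the chi-squared or Fisher test as supporting, and state whether the threshold of 5 refers to observed or expected counts.
- State that a non-significant test will not be read as absence of excess rebreathing, and that the report will give the largest excess not excluded.

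No non-inferiority margin is required. The trial is a superiority trial and makes no non-inferiority claim for this outcome.

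The cost is a few sentences and a few lines of code, with no extra patients or data. The downside is a less favourable safety statement: with 60 per arm and an uncommon event, the upper limit will probably leave a several-fold excess open.

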### Interim analyses {21b}

Due to the moderate size of the trial and because we are pragmatically evaluating conventional therapies in current use in our healthcare system, no interim analysis is planned.

### Methods for additional analyses (e.g. subgroup analyses) {20b}

Because baseline characteristics may be skewed between the two groups despite randomisation, we will also perform adjusted analyses for (a) the primary outcome of VFD using competing risks regression and (b) for the secondary outcome of 28- or 180-day survival using Cox regression. Since we are expecting only ~ 26 events (calculation: 60*(1/3*0.674 + 2/3*0.081) + 60*(2/15*0.674 + 13/15*0.081)), we are limited to few co-variates to avoid overfitting. We plan to adjust for age (cont.), Clinical Frailty Index (cont.) and NEWS score at randomisation (cont.). If other baseline characteristics appear severely skewed instead, we may consider adjusting for other co-variates, such as gender, comorbidities (Charlson comorbidity index), BMI, smoking, Nordic origin of birth or serum biomarkers (e.g. lactate, serum D-dimer, lymphocyte count).

### Methods in analysis to handle protocol non-adherence and any statistical methods to handle missing data {20c}

The analyses of the primary and secondary outcomes will be analysed as randomised, regardless of protocol adherence. Analyses according to adherence will be considered if important deviations from the protocol compromise the validity of the “as randomised” analysis. All variables will be screened for frequency and type of missingness (i.e. missing at random or not). Multiple imputation will be used if missingness is above 5% in any variable. In the case of missing data and imputation, complete case analysis will be performed as a sensitivity analysis.

### Plans to give access to the full protocol, participant-level data and statistical code {31c}

We plan to publish the statistical code as a supplement to the main manuscript publication. Participant-level data can be accessed from the principal trial investigator on reasonable request.

### Composition of the data monitoring committee, its role and reporting structure {21a}

Because this is a pragmatic trial of moderate duration comparing medical devices in daily use, we have not considered there to be a need for a data monitoring committee.

### Adverse event reporting and harms {22}

The Swedish Medical Products Agency (Läkemedelsverket) has reviewed the study design in May 2020 and concluded that it should not be considered a clinical trial in the traditional sense but rather a pragmatic randomised study between two approved medical devices. Hence, reporting of adverse events will not be as ambitious as a clinical trial testing a novel drug. We will aim to evaluate any harm from the intervention in our primary and secondary endpoints on survival, intubation frequency, carbon dioxide rebreathing and patient-reported comfort. There is also a commentary section in the study-specific CRFs where study nurses can report allocation violations or any unexpected side-effects from allocated intervention.

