### Criteria for discontinuing or modifying allocated interventions {11b}

There are no mandated criteria for discontinuing or modifying allocated interventions, but the patient and the treating physician may choose to do so at any time, upon which they will be asked to report timing and reason for non-adherence. Patients moving to the ICU due to deterioration or to a regular ward due to clinical improvement will be able to adhere to the standard protocol follow-up. In the (improbable) event of a patient being moved while having an unchanged need for respiratory support to another hospital or ward that does not have the treatment device available allocated to the patient (i.e. Helmet CPAP), we will regard this as an allocation violation, but we should still be able to assess the primary outcome on an “as randomised”-basis. Patients on the Helmet CPAP will necessarily have to take off the Helmet for shorter periods of time during meals. We will actively register the number of hours spent in each device each day on a case report form (CRF) as a continuous evaluation of allocation adherence. More than 6 h per 24 h off the allocated device will be registered as an allocation deviation.

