### Data management {19}

Screening and baseline data will be entered live using an eCRF at the time of randomisation. Further data on primary and secondary outcomes will be entered into the REDCap database collectively after all patient recruitment has finished, using filled-out paper CRFs and electronic health records. Individual patient data will be handled as ordinary chart records and will be kept according to the European General Data Protection Regulation (GDPR). All original records (e.g. consent forms and CRFs) will be retained at the Department of Infectious Disease in Helsingborg Hospital for 15 years to allow inspection by relevant authorities. The coded trial database will be maintained for 15 years if requested for revision.

**Table 1 Tab1:** Data collection flow chart

Timing	Method	Data type and specification
At screening	eCRF (RedCap)	Inclusion and exclusion criteria and informed consent
At randomisation	eCRF (RedCap)	Allocation, treatment limitations (i.e. ICU admission), weight, height, place of birth, smoking, date of symptom start, gender, clinical frailty scale, mode of respiratory support, SpO2%, litres O2/min, RR/min and NEWS
One hour post randomisation	CRF paper	SpO2/FiO2-ratio
24 h post randomisation	CRF paper	Patient comfort (visual analogue scale (VAS) 1–10)
Daily for 28 days	CRF paper	Mode of respiratory support, number of hours per 24 h in allocated support, nr of hours in prone position per 24 h, NEWS, PEEP or Flow, SpO2%, RR/min and events with commentary (e.g. allocation violation, death, exit from study, ICU admission or hospital discharge)
Retrospectively from electronic medical charts	eCRF (RedCap)	Comorbidities, vitals, medications, radiology, microbiology and laboratory parameters at triage, randomisation and during hospital stay, and, duration of hospital stay, duration of ICU stay, duration of mechanical ventilation and days alive within 28 and 180 days, respectively.

*Abbreviations*: *eCRF* electronic case report form, *ICU* intensive care unit, *SpO2%* peripheral oxygen saturation, *L O2/min* litres of oxygen per minute, *RR* respiratory rate, *NEWS* national early warning score, *FiO2* fraction of inspired oxygen, *PEEP* positive end-expiratory pressure

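### Tolerance is named as a main harm of the helmet, but the fixed harm evaluation covers it only by one comfort score at 24 h, and no between-arm comparison of stopping the device for intolerance is planned

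*Protocol article*

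**What the plan says.** All references are to the protocol article.

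- **Which harms matter.** The outcomes rationale under {12} says that carbon dioxide rebreathing "is the main harm apart from death and comfort/tolerance issues that can be considered more likely for the intervention group than the control group". Tolerance is therefore one of three harms singled out, with death and rebreathing. The same paragraph says comfort may carry particular weight if superiority is not shown or the effect is small.
- **Where harm is evaluated.** Section {22} says the trial will "evaluate any harm from the intervention in our primary and secondary endpoints on survival, intubation frequency, carbon dioxide rebreathing and patient-reported comfort". It adds a free-text comment field on the CRF, with no analysis attached.
- **How comfort is measured.** Outcomes {12} and Table 1 give one VAS score from 1 to 10 at 24 h after randomisation. Section {20a} compares it by the Mann-Whitney U test. Comfort is not in the daily row of Table 1.
- **What is recorded about stopping.** Under {11b}, the patient or the treating physician may leave the allocated device at any time, and "they will be asked to report timing and reason for non-adherence". Hours in each device are registered daily "as a continuous evaluation of allocation adherence". Table 1 lists "number of hours per 24 h in allocated support" in its daily row.

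**The concern.** The most direct evidence on tolerance is whether patients stay on the device and, if not, why they leave it. The trial collects this, but the harm evaluation does not use it. A helmet patient who gives an acceptable score at 24 h and later gives up the helmet because it cannot be endured, without being intubated or dying, counts in none of the harm endpoints.

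The early score has a gap of its own. The article does not say how comfort is handled for a patient who has left the allocated device before 24 h. Because section {20c} analyses outcomes as randomised, such a patient's score could describe another form of support and still count for the helmet arm.

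The loss would be greatest in the case the protocol itself anticipates: no superiority or a small effect on ventilator-free days, so that the choice of device turns on tolerability.

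**Working it through.** **Is any comparison of stopping planned?** The sections that define, collect or analyse tolerance, device use or harm were set side by side.

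| Section | Content | Compares stopping for intolerance between arms? |
|---|---|---|
| {12} Outcomes | VFD, SpO2/FiO2 at 1 h, comfort at 24 h, intubation, rebreathing, days alive | No |
| {20a} Methods | Tests for those outcomes | No |
| {20b} Additional analyses | Adjusted VFD and survival models | No |
| {20c} Non-adherence | Adherence analyses considered if deviations threaten validity | No; conditional, and for another purpose |
| {22} Harms | Four endpoints plus free text | No |
| {11b}, Table 1 | Timing and reason for stopping; daily hours | Data only |

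**What do the listed endpoints catch?**
- Intolerance followed by intubation: caught indirectly by intubation frequency and VFD.
- Intolerance followed by death: caught indirectly by VFD and survival.
- Discomfort present at 24 h: caught by the VAS, if the patient is still on the device.
- Intolerance that ends only in leaving the allocated device: not caught.

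**How many patients could this be?** No intolerance rate is given, so the rates are assumptions. With 60 per group ({14}):
- 5%: 0.05 × 60 = 3 helmet patients
- 10%: 0.10 × 60 = 6
- 20%: 0.20 × 60 = 12

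**How precise would a comparison be?** Assume 5% stop for intolerance on HFNC. The 95% CI half-width is 1.96 × √[p₀(1−p₀)/60 + p₁(1−p₁)/60]. Two-sided power at 0.05 is by the normal approximation.

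| HFNC | Helmet | Half-width (percentage points) | Power |
|---|---|---|---|
| 5% | 10% | 9.4 | 0.18 |
| 5% | 15% | 10.6 | 0.45 |
| 5% | 20% | 11.5 | 0.70 |
| 5% | 25% | 12.3 | 0.88 |
| 5% | 30% | 12.8 | 0.96 |

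First row: 1.96 × √(0.0475/60 + 0.09/60) = 1.96 × 0.0479 = 0.094. Power is modest unless the difference is large, so the result should be read as an estimate with its interval.

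The sample size does not bear on this point.

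**The case against.** The strongest reply is that an article need not list every table. Discontinuation by arm with reasons is routine content of an analysis plan, the data are provided for, and {22} does not say that nothing else will be reported. A reader might infer that intolerance will never be compared, or that the stopping data serve adherence monitoring alone. The text supports neither. The adherence purpose is stated for the daily hours, not for the timing and reason, and an analysis plan that is not shown may tabulate both. What remains is that {12} and {22} do fix the outcomes and the endpoints that carry the harm evaluation, and a harm the protocol ranks among the main ones has its direct measure outside them.

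It can also be said that one early score is defensible in a trial that deliberately keeps data collection small: comfort needs an awake, participating patient, and a fixed 24 h point limits losses to intubation or discharge. That stands, and it is why the score should be kept.

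Two numerical arguments are tempting and should not be used.
- The 2.3 days in {14} might be read as showing that over half of device use follows the 24 h score. That figure is ward time before intubation, not time on the device, and it applies only to patients later intubated.
- An example of 6 versus 0 stops gives Fisher p = 0.027, but 5 versus 0 gives 0.057 and 6 versus 1 about 0.11. Section {11c} says HFNC flow can also be uncomfortable, so zero stops on HFNC cannot be presumed.

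Nor would a diluted primary result be impossible to interpret: {11b} collects the data and {20c} allows an adherence analysis, though only conditionally.

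**Conclusion.** The point holds within limits. In this document, tolerance enters the harm evaluation only through one VAS score at 24 h, and no between-arm comparison of stopping for intolerance is planned, although its timing and reason are recorded. The gap concerns patients who leave the allocated device for intolerance without being intubated or dying, and 24 h scores from patients already off the device. Its size cannot be derived from the documents; 3 to 12 of 60 helmet patients rests on assumed rates of 5% to 20%. The primary analysis is unaffected. The change is worth making because tolerability would weigh most if superiority is not shown.

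**What to change.** In {12} and {22}, add a harm outcome: the proportion in each arm who stopped the allocated device for discomfort or intolerance within 28 days, taken from the timing and reason recorded under {11b}. Analyse it as randomised and give the risk difference with 95% CI. Optionally add cumulative incidence with intubation, death and end of respiratory support as competing events. State that it is an estimate and not a powered test. Keep the 24 h VAS, and report how many in each arm had already left the allocated device when it was taken.

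The cost is a sentence in each section and one extra analysis, with no new visit, patients or clinical rule. The definition needs some care: short breaks such as meals must be kept apart from stopping, and free-text reasons must be coded, preferably blind to outcome. The reason comes from unblinded patients and staff, so the result should be presented as a harm and not as evidence on efficacy.
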